### Interim analyses {21b}

One major interim analysis is planned after complete data collection of the 12th patient. A complete review of complications during mechanical ventilation and postoperative complications will be done with a special focus on intervention-associated complications. If any identified complications could be associated with this investigation, recruitment will be temporarily suspended until further actions are discussed with the local ethics committee. During the whole investigation postoperative pulmonary events will be monitored. All patients will be screened electronically 7 days after joining the study. If there are any study-related complications identified, this will be reported immediately to the study director. Further actions will then be taken as needed. If serious adverse events will be detected during the investigation, the study director will quickly inform the Ethics Committee. Patient recruitment will stop until the issues are clarified.

### Methods for additional analyses (e.g., subgroup analyses) {20b}

There are no additional analyses planned.

### Methods in analysis to handle protocol non-adherence and any statistical methods to handle missing data {20c}

If data for the primary outcome is missing at the conclusion, exceeding the number of the expected drop-out rate, additional patients will be recruited after agreement of the local Ethics Committee. Missing data of other variables will not be supplemented.

### Plans to give access to the full protocol, participant level-data and statistical code {31c}

Due to the sensitivity of patient data, access to full protocol, participant level-data and statistical codes will be provided in anonymized form after reasonable request. The complete study protocol will be shared on reasonable request.

### Composition of the data monitoring committee, its role and reporting structure {21a}

In accordance with the local Ethics Committee a Data Monitoring Committee is not necessary for this study due to its low risk for participants.

### Adverse event reporting and harms {22}

Adverse events will be reported to the study leader and evaluated particularly with regard to study-related measures. Serious events will be reported to ethics committees if required, and documented in the study files for review.

### Frequency and plans for auditing trial conduct {23}

An official auditing is not required for this trial.

### Plans for communicating important protocol amendments to relevant parties (e.g., trial participants, ethical committees) {25}

Important protocol changes will be announced to the local Ethics Committee as an amendment by the director of the study. All changes will be recorded.

### Dissemination plans {31a}

The results of the study will be shared at scientific conferences and published in scientific journals. The rules for Good scientific practice and Good scientific practice authorship will be respected.

## Discussion

Despite recent advances, mechanical ventilation is still an unphysiological transfer of mechanical energy from the ventilator to patient’s lungs, which necessitates further improvement. Furthermore, detecting and discriminating even small improvements in mechanical ventilation is challenging, because so far, no sensitive biological parameters were identified, which reliably reflect mechanical load on the respiratory system and its consecutive biological trauma. This study aims to address this gap by evaluating pressure-controlled ventilation with volume guarantee using a reduced inspiratory flow rate. The reduction will be achieved by increasing the inspiratory ramp time, a simple modification, for which unpublished preliminary data from a physical model suggests that it may reduce peak wall shear stress in the airways, smoothen alveolar stretch, and decrease the mechanical load transferred to the lungs. Even though many studies on lung-protective ventilation mention the reduction of flow rate as a potential target [1–8], only limited data of clinical trials exist. One reasonable cause might be that reduced inspiratory flow affects the inspiration, reflecting only one third to one half of the whole breathing cycle. Thus, its overall impact on lung-protective ventilation may have only minor contribution to lung-protective ventilation. However, because reducing inspiratory flow rate is very easy to accomplish without any modifications of the ventilator by increasing the inspiratory ramp time during pressure-controlled ventilation, we consider it a promising target, even if only small effects are expected. To quantify the mechanical consequences of this modification, mechanical power will be used as the primary measure of mechanical load transferred from the respirator to the respiratory system. Mechanical power seems to be the most suitable value to detect and discriminate even small changes in transferred mechanical load [1, 3]. In addition, we will investigate several lung-specific proteins in patient’s blood to improve the biological assessment of mechanical load and potential ventilator-associated injury.The analyses of the kinetics of these lung-specific proteins and their concentration in combination with the results of the calculated mechanical energy transferred to the lungs might facilitate detecting a more suitable biological parameter, representing mechanical load of the lungs. The selected markers include sRAGE [15, 16] and GDF-15 [17], which are among the most extensively studied but not fully lung-specific proteins; HTI-56 as a marker of typ-I pneumocytes [18, 19], KL-6 and SP-D as markers of type-II pneumocytes [20] and CCP-16, representing the bronchioles [21]. This selection of proteins may also help to identify the anatomical region of pulmonary injury. However, pulmonary damage is subjected to a complex and multifactorial pathogenesis, where even a non-pulmonary inflammatory reaction could promote lung damage [22, 23]. Therefore, we investigated patients receiving neurosurgery to obtain a long time of mechanical ventilation with limited surgical tissue trauma. Furthermore, to control inflammatory response, IL 6 and PCT will be measured to quantify systemic inflammatory reaction.

Beyond biological markers and mechanical power, our study will evaluate respiratory system mechanics, Horowitz index, distribution of ventilation, and postoperative pulmonary complications, to cover a broad range of relevant outcomes and potential differences between the two ventilation strategies.

We are aware of several limitations. First, the number of patients is small. However, this first trial focuses on perioperative feasibility and the safety of ventilation modification while conserving resources and minimizing patient risks. If the study results suggest clinically relevant benefits, an extended multicenter investigation will be planned. Second, blinding of the data collector and the attending anesthetist is not possible, which may influence perioperative management or data completeness. Nevertheless, mechanical ventilation will be strictly implemented according to the study protocol. Data recording will be independent, and all analyses will be performed under blinded conditions. Third, besides inspiratory ramp time, the two ventilation strategies differ in the inspiratory-to-expiratory time ratio. Therefore, differences in the mechanical load cannot be attributed solely to the inspiratory ramp time. However, we deliberately chose a reduced inspiratory-to-expiratory time ratio in the study group to facilitate the longest possible inspiratory ramp time to accentuate differences. We are aware that this point must be taken into account in any conclusion. Fourth, the selection of lung-specific proteins is limited. However, additional markers will be analyzed if the planned analysis is inconclusive.

Besides inspiratory ramp time, the two ventilation strategies differ in the inspiratory-to-expiratory time ratio. Therefore, differences in the mechanical load cannot be attributed solely to the inspiratory ramp time. However, we deliberately chose a reduced inspiratory-to-expiratory time ratio in the study group to facilitate the longest possible inspiratory ramp time to accentuate differences. We are aware that this point must be taken into account in any conclusion.

In conclusion, this trial investigates a simple modification aimed at reducing inspiratory peak flow as another potential component of lung-protective ventilation. By combining mechanical measurements with detailed biological profiling, the study aims to improve the assessment and discrimination of lung-protective ventilation. This research could therefore lead to a new easily applicable form of lung-protective ventilation. Identifying a lung-specific protein, which represents mechanical load of the lungs could improve risk-stratification and diagnosis or therapy of patients with lung damage.

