### Trial design {8}

The study design is reported in accordance with the SPIRIT 2013 Checklist. This is an exploratory pilot study that is monocentric, prospective, randomized, and controlled with blinded patients, unblinded data collectors and blinded evaluators. The study is conducted at the Department of Anesthesiology and Critical Care, Medical Center – University of Freiburg and has been approved by the local Ethics Committee of the University of Freiburg (24-1273_S1/24-1273_1-S1). The trial complies with the principles of the Declaration of Helsinki and the principles of Good Clinical Practice.

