## Intervention description {11a}

### Ventilation protocol

In this study, patients will receive a pressure-controlled ventilation with volume guarantee with a tidal volume of 8 ml∙kg^−1^ of predicted body weight, with an inspiratory oxygen fraction between 0.3 and 0.5. The breathing rate will be adjusted to maintain end-expiratory carbon dioxide partial pressure in the range of 32 to 45 mmHg. Positive end-expiratory pressure will be set at 7 cmH_2_O for all patients. Patients of the intervention group will be ventilated with the longest available inspiratory ramp time permitted by the ventilator and with an inspiratory-to-expiratory time ratio of 1:1 to 1:1.2 to facilitate the longest possible inspiratory ramp time. Patients of the control group will be ventilated with a short inspiratory ramp time (0 s) with an inspiratory-to-expiratory time ratio of 1:1.9 to 1:2.1.

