## Assignment of interventions: allocation

### Sequence generation {16a}

Participants will be randomly assigned to one of two groups: Ventilation with an increased inspiratory ramp time (study group) or ventilation with a short inspiratory ramp time (control group). Randomization will be done in a 1:1 ratio. The assignment will not depend on any patient factors. A computer-generated block randomization with blocks containing 2 to 6 patients will be used to create a random grouping sequence. The study team will have no access to the randomization list.

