## Assignment of interventions: blinding

### Who will be blinded {17a}

During the intervention period, only the patients will be blinded to group allocation. The attending anesthesiologist will necessarily be unblinded during mechanical ventilation but will not be involved in data collection or analysis. Blinding of the data collector will not be feasible in the perioperative period due to his task to ensure adherence to the ventilation protocol. The data collector will take the blood samples and record the ventilation data and the EIT data. The assessor evaluating postoperative pulmonary complications will be blinded to group assignment. All recorded data and all blood samples will be labeled with pseudonyms that do not reveal group assignment, ensuring laboratory personnel and outcome assessors will be blinded. Only during the final overall evaluation can the connection to the group membership be traced back.

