### Data management {19}

The data sources include the anesthesia protocol, measured variables (such as ventilation parameters, Horovitz-index and EIT data), and measured protein concentrations. Patient records are also part of the data sources. The data collected in this study are recorded and processed digitally. Patient and disease information is handled confidentially, following data protection laws. These data are stored in a pseudonymized form. Patient data and study data are kept separate from each other. Allocation lists and signed consent forms are stored in different folders on site. Only medical and scientific staff involved in the study can access it.

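### The blanket statement that analyses and evaluators are blinded cannot hold for mechanical power, mean airway pressure and compliance, because the recorded curves themselves show the arm

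*Protocol article*

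**What the plan says.** Two places make a general claim. Trial design {8} describes a trial with "blinded patients, unblinded data collectors and blinded evaluators". The limitations part of the Discussion concedes that the data collector and the attending anesthetist cannot be blinded, and then answers that recording will be independent and that "all analyses will be performed under blinded conditions".

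The means is given in Who will be blinded {17a}: "All recorded data and all blood samples will be labeled with pseudonyms that do not reveal group assignment". The same section adds that the link to group membership can be traced at the final overall evaluation.

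The Ventilation protocol sets the arms apart. Control patients are ventilated with a "short inspiratory ramp time (0 s) with an inspiratory-to-expiratory time ratio of 1:1.9 to 1:2.1". Intervention patients get the longest ramp the ventilator permits, "with an inspiratory-to-expiratory time ratio of 1:1 to 1:1.2 to facilitate the longest possible inspiratory ramp time".

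Plans for assessment and collection of outcomes {18a} derives the primary endpoint from continuous flow and pressure recordings processed in Matlab: power for each breath, after removing tube resistance, then a mean over all of the ventilation time. Mean airway pressure and compliance are also calculated breath by breath.

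On lists, Sequence generation {16a} says "The study team will have no access to the randomization list". Data management {19} keeps allocation lists and consent forms in separate on-site folders and continues "Only medical and scientific staff involved in the study can access it". Confidentiality {27} restricts the pseudonym list to the study director.

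**The concern.** A pseudonym hides the arm only if the data behind it do not give the arm away. That works for a serum sample. It does not work for a pressure and flow recording when the intervention is the shape and timing of the pressure and flow. Whoever opens such a file to process or check it can see the allocation.

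This matters because the Discussion uses blinded analysis to offset an admitted weakness, namely that unblinded staff may influence management or data completeness. A reader would credit the primary endpoint with a protection it does not have. The Discussion also expects only small effects, so the reader has reason to ask how data handling is protected.

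**Working it through.** The blinding claim rests on no figure in the plan, so there is none to reproduce. The check has three parts: whether the arms can be told apart in the curves, whether the blinding statements agree with each other, and whether the list-access statements agree.

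**1. Can the arm be read from a breath?**

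Inputs are the inspiratory-to-expiratory ratios in the Ventilation protocol. For a ratio of 1:E, the inspiratory share of the breath cycle is 1/(1+E).

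| Arm | Ratio | Calculation | Inspiratory share |
|---|---|---|---|
| Intervention | 1:1 | 1/2.0 | 50.0% |
| Intervention | 1:1.2 | 1/2.2 | 45.5% |
| Control | 1:1.9 | 1/2.9 | 34.5% |
| Control | 1:2.1 | 1/3.1 | 32.3% |

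The intervention range is 45.5–50.0% and the control range 32.3–34.5%. The smallest gap is 45.5 − 34.5 = 11.0 percentage points. Timing alone therefore separates the arms for any breath delivered per protocol. The ramp (0 s against the longest possible) is a second marker in the same recording.

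**2. Do the blinding statements fit together?**

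- Discussion: every analysis is blinded.
- Trial design {8}: evaluators are blinded, without exception.
- Who will be blinded {17a}: labels hide the group, but the group can be traced at the final evaluation. An analysis in which the group is known is an exception to the Discussion's statement.
- Statistical methods {20a}: results are analysed as treated, so someone must establish at analysis which ventilation each patient received.

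The outcomes affected are those taken from the ventilation curves: mechanical power, mean airway pressure and compliance change. For laboratory proteins and the blinded assessment of pulmonary complications, the curves do not break the blind.

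**3. Do the list statements fit together?**

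Sequence generation {16a} denies the study team the randomization list. Data management {19} mentions allocation lists and then gives study staff access to something referred to in the singular, which may be the lists, the folders or the stored data in general. If the allocation lists are the randomization list and are meant, this conflicts with {16a}. If they are the pseudonym key and are meant, it conflicts with Confidentiality {27}. If neither is meant, the sentence needs a clear subject.

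**The case against.** The strongest reply is that little harm can follow. The endpoint is an area computed from machine-recorded signals, not a rating. Section {18a} takes each breath and averages over all of the ventilation time, with tube resistance removed as part of the calculation. The ANCOVA uses one mean per patient, and group labels can be coded at that step. Section {17a} already says who is unblinded and names the laboratory personnel, outcome assessors and complication assessor as blinded. On this view only an over-broad sentence in the Discussion and one word in {8} are at fault.

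Most of that stands, and it limits the point. Two stronger readings are tempting and should not be drawn.

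- *That visible arms leave the choice of breaths open to bias.* The article describes no selection of breaths and no manual, file-by-file decisions. Rules for artefacts or disconnections may well sit in a fuller document that is not shown, and their absence from an article is no fault.
- *That the analysts hold the allocation.* The wording in {19} is ambiguous, and {16a} and {27} point the other way. Some staff must know past assignments in any case, because under Implementation {16c} the data collector opens each envelope. A record of past assignments is not the randomization list. This is wording to reconcile, not evidence of a broken blind.

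The reply does not rescue the statement itself. Coding the groups for the ANCOVA does not blind the step that turns curves into the number analysed. An objective measurement is a good argument that blinding matters less here, but the Discussion does not make that argument; it claims the blinding.

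**Conclusion.** The claim is wrong as written for mechanical power, mean airway pressure and compliance. The arm is identifiable from any protocol-compliant breath, with inspiratory shares of 45.5–50.0% against 32.3–34.5%, and {17a} itself provides for group membership to be known at the final evaluation.

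The size is modest. No bias in mean mechanical power is shown or quantified, and no figure in the plan changes. The trial is not invalidated; the loss is a safeguard that the Discussion relies on.

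The conclusion assumes that ventilation stays within the stated ratios and that at least one person who processes or checks the files can look at the curves. If processing were fully automated under fixed rules, the practical exposure would be small, but the protection would then come from the fixed rules and should be described that way.

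**What to change.** 1. Restate Trial design {8}, Who will be blinded {17a} and the Discussion so that blinding covers patients, laboratory staff and the complication assessor, and expressly not the processing of ventilation curves. Make the Discussion agree with {17a} on the tracing of group membership at the final evaluation.
2. In place of the blinding claim, state that a single processing script, including the tube correction, is locked before the curve files are analysed and run unchanged on all of them. Report the share of breaths excluded, if any, by arm. Naming the tube correction is useful because Primary endpoint lists mechanical power both with and without it, whereas {18a} describes only the corrected value.
3. Reconcile Data management {19} with Sequence generation {16a} and Confidentiality {27}: say what the allocation lists are, and who may open each list and when.

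The cost is protocol wording and an earlier script lock; sample size and visits do not change. Trial status reports one-third of patients enrolled at the time of writing, so a lock before analysis may still be possible, and the wording can be corrected at any time. The downsides are a less favourable statement on blinding and that unusual breaths are handled by rule instead of by eye.

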### Trial status

Protocol version 2.0 was approved by the local ethics committee on 17 September 2024 and version 3.0 including an amendment was approved on 14 August 2025. Patient recruitment began on 2nd September 2025. At the time of writing the manuscript, one-third of patients were successfully enrolled. Recruitment is expected to be completed by February 2026.

## Data Availability

The datasets used and/or analyzed during the present study are available from the corresponding author on reasonable request.

## Abbreviations

CCP16: Clara cell protein 16
EIT: Electrical impedance tomography
ELISA: Enzyme-Linked Immunosorbent Assay
GDF-15: Growth differentiation factor 15
IL-6: Interleukin 6
HTI56: Human type I cell-specific apical membrane protein
KL6: Cancer of the lungs-6
PCT: Procalcitonin
SP-D: Surfactant protein D
sRAGE: Soluble receptor for advanced glycation end products
